#### **24.Data analysis**

Data will be analyzed in this study using GraphPad Prism software to ensure accuracy and consistency of results. For baseline characteristics data, patients' age, gender, admission time, and disease-related clinical information will be descriptive statistics, Categorical variables will be presented as frequencies and proportions, whereas normally distributed continuous variables will be described using means and standard deviations. For non-normally distributed data, descriptive statistics will utilize median and percentile values (P25 and P75). Between-group comparisons will be carried out using t-tests, analysis of variance, chi-square tests, Mann-Whitney U tests, and statistical methods for repeated measures data to assess differences among the groups. The significance level in this study will be set at  $\alpha=0.05$ , with  $P<0.05$  indicating statistical significance.

The changes in the primary outcome indicator VAS-P at different time points (0h, 1h, 6h, 12h, 24h, 48h, 72h) will be assessed by repeated measures analysis of variance (ANOVA) if the data conform to a normal distribution. Secondary outcome indicators, such as intra-abdominal pressure (IAP), will be analyzed in the same manner. The number of additional interventions (NAI) and the dose of coadministered medication (DCD) will be expressed as mean  $\pm$  SD or median (IQR), and comparisons between groups will be made using the t-test or the Mann-Whitney test. The number of days of epidural placement (NDEP) will also be subjected to descriptive statistics and between-group comparisons. The number of cases of adverse events (AE) will be expressed as frequency, and comparisons between groups will be made using the chi-square test or Fisher's exact test. The outcome indicators, including puncture success rate (PSR), length of stay in the ICU (ICU-LOS), 28-day mortality rate (28D-MR), and satisfaction with analgesic effect score (SAE), will be subjected to descriptive statistics and between-group comparisons using the chi-square test or Fisher's exact test, as well as the t-test or the Mann-Whitney test.

In this study, faced with the problem of missing data, we would first try to obtain the missing data through retrospective collection. If this approach fails to work, we will take appropriate measures to deal with the problem depending on the nature of the missing data. For random missing data from consecutive repeated measurements, we can estimate this by calculating the average of the time points before and after the missing

data. If data are missing on two consecutive occasions, the patient's data are considered incomplete and the patient will be excluded. For data that are not missing at random, we will choose an appropriate interpolation method, such as the maximum deviation method or the Verbeke and Molenberghs method, on a case-by-case basis. When choosing interpolation methods, we will consider the distributional characteristics of the data and the missing mechanism to ensure the reliability and validity of the interpolation results.

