## 12. Sample size

This study is a randomized controlled trial, and the primary outcome indicator is the VAS-P score. From the literature review, it is known that the mean VAS-P scores after the intervention of similar control group protocols are 1-3, and there is no study similar to the experimental group, and the mean VAS-P scores of the pre-experimental group are 1-2. It is proposed to formulate the standard deviation of the two groups combined  $\sigma = 2.5$ , and it is expected that the pain symptom scores of the experimental group can be decreased by  $\delta = 2$ . Setting a bilaterality of  $\alpha = 0.05$ , the degree of certainty is 90%, and based on the formula of the sample size [Formula 1](#), the sample size is calculated for each group of  $N = 33$  participants. Assuming a 15% dropout rate, a total of 76 participants were needed based on a 1:1 randomization ratio.

*Formula 1:*

$$n = \frac{2(z_{\alpha} + z_{\beta})^2 + \sigma^2}{\delta^2}$$

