## **19.Primary outcome measure**

Visual Assessment Scale-Pain (VAS-P): which consists of a 100-mm straight line, with one end indicating “no pain at all” and the other end indicating “the most severe pain imaginable”, with the patient marking the corresponding position on the line to represent his/her pain level. Patients marked the corresponding position on the line to represent their pain level. The data were collected by the data collectors at the specified time points (0h, 1h, 6h, 12h, 24h, 48h, 72h). Among them, 0h was before epidural placement, and the other times were 1h, 6h, 12h, 24h, 48h and 72h after epidural placement.

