| Visual Analog Scale for Pain(VAS-P)              |                 |            | X               | X              | X              | X              | X              | X              | X              | X              |                |                |                |           |
| Intra-abdominal pressure(IAP)                    |                 |            | X               | X              | X              | X              | X              | X              | X              | X              |                |                |                |           |
| Number of additional interventions(NAI)          |                 |            |                 |                |                |                |                | X              | X              | X              |                |                |                |           |
| Dosage of combined drugs(DCD)                    |                 |            |                 |                |                |                |                |                |                |                | X              |                |                |           |
| Number of days of epidural placement(NDEP)       |                 |            |                 |                |                |                |                |                |                |                | X              |                |                |           |
| Puncture-related adverse events                  |                 |            |                 |                |                |                |                |                |                |                |                |                |                |           |
| Drug-related adverse events                      |                 |            |                 |                |                |                |                |                |                |                |                |                |                |           |
| Puncture surgery rate (PSR)                      |                 |            | X               |                |                |                |                |                |                |                |                |                |                |           |

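### The primary VAS-P analysis treats the pre-placement score as an outcome level, names no deciding test, and depends on a normality condition that the plan's own figures make unlikely

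*Protocol*

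**What the plan says.** Section 24 (Data analysis) lists VAS-P at 0h, 1h, 6h, 12h, 24h, 48h and 72h and says that its changes "will be assessed by repeated measures analysis of variance (ANOVA) if the data conform to a normal distribution". Intra-abdominal pressure (IAP) is to be analysed the same way. Section 19 defines the first of these times: "Among them, 0h was before epidural placement".

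Section 24 states no baseline adjustment and no deciding test. It gives a rank-test alternative for the number of additional interventions and the drug dosage, but none for VAS-P. An earlier sentence there lists t-tests, ANOVA, chi-square, Mann-Whitney and unspecified repeated-measures methods for between-group comparisons in general.

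Section 12 (Sample size) rests on a single difference between two means, with no time point attached: "it is expected that the pain symptom scores of the experimental group can be decreased by" 2 points, with a "standard deviation of the two groups combined" of 2.5. It also reports that "the mean VAS-P scores after the intervention of similar control group protocols are 1-3".

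In the Section 35 schedule, the row beginning "Visual Analog Scale for Pain(VAS-P" has eight marks, one of them at 3h. Sections 19 and 24 have no 3h assessment.

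**The concern.** Three features combine.

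- **No deciding test.** A repeated-measures ANOVA with a group factor gives a group effect, a group-by-time interaction and, through follow-up tests, time-point differences. If any of them can be called primary, the 5% error rate is not held.
- **0h as an outcome level.** Randomisation makes the arms equal in expectation at 0h. If the group effect decides, including 0h shrinks a constant effect to 6/7 of its size, and the information in the baseline is not used to reduce variance.
- **A normality condition with no VAS-P fallback.** If the condition fails, the primary method has to be chosen with the data in view.

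Only the protocol is at hand, and a statistical analysis plan may add detail. But the protocol itself fixes the method, its levels and its condition. The schedule contradicts even the set of levels.

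**Working it through.** **1. The plan's own figure.** Inputs from Section 12: two-sided alpha 0.05, power 90%, difference 2, SD 2.5.

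n = 2(1.960 + 1.282)² × 2.5² / 2² = 32.8, so 33 per arm. 66 × 1.15 = 75.9, so 76 in total. Both stated figures reproduce. (Formula 1 as printed adds the variance instead of multiplying by it and would give 6.8, which looks like a misprint.) The 33 belongs to one two-sample comparison of means, which Section 24 does not name as the primary test.

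**2. The normality condition.** For a normal distribution with SD 2.5, the share below zero is Φ(-mean/2.5):

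- mean 1: Φ(-0.4) = 34%
- mean 2: Φ(-0.8) = 21%
- mean 3: Φ(-1.2) = 12%

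The scale cannot go below zero. With simulated bounded scores (beta distribution on an assumed 0-10 range, 33 per sample), a Shapiro-Wilk test rejects in 100%, 100% and 87% of samples at means 1, 2 and 3 with SD 2.5. With an assumed SD of 1.5 it rejects in 100%, 77% and 21%.

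**3. Error rate.** The main effect and the interaction are nearly independent under the null, so success on either gives about 1 - 0.95² = 9.75%. Simulation gives 10.4%, 10.2% and 9.9% at correlation 0.3, 0.5 and 0.7.

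**4. Power.** Assumptions: 33 per arm, SD 2.5 at every time, exchangeable correlation r (not given in the protocol), and a constant difference δ at all six post-placement times.

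- Group effect with 0h: difference 6δ/7, variance per patient σ²(1 + 6r)/7, 64 df.
- Interaction with 0h: noncentral F(6, 384), λ = (33/2)(6/7)δ² / [σ²(1 - r)].
- Post-placement mean adjusted for 0h: difference δ, variance per patient σ²[(1 + 5r)/6 - r²], 63 df.

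Example at r = 0.5, δ = 2:

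- Group effect: SE = 2.5√(0.571 × 2/33) = 0.465, and 1.714/0.465 = 3.69, giving 95.2%.
- Interaction: λ = 16.5 × 0.857 × 4/3.125 = 18.1, giving 90.7%.
- Adjusted mean: SE = 2.5√(0.333 × 2/33) = 0.355, and 2/0.355 = 5.63, giving over 99.9%.

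| Test | δ = 2; r = 0.3 / 0.5 / 0.7 | δ = 1; r = 0.3 / 0.5 / 0.7 |
|---|---|---|
| Group effect with 0h | 99.1 / 95.2 / 88.9% | 58.3 / 44.2 / 35.7% |
| Interaction with 0h | 76.7 / 90.7 / 99.3% | 21.7 / 30.0 / 49.5% |
| Post-placement mean, adjusted for 0h | all above 99.9% | 79.9 / 79.1 / 88.1% |

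The 1-point column is relevant because Section 12 expects means of 1-3 under control-type regimens and 1-2 in its pre-experimental group. A 2-point gap arises only at the extremes, 3 against 1.

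**5. Two sensitivity checks.**

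- *Weaker baseline correlation.* Entry requires VAS-P above 3, which restricts the baseline range. With an assumed baseline correlation of 0.3 and 0.5 among later scores, the variance factor is 3.5/6 - 0.09 = 0.493. The SE is 0.432, and power for the adjusted mean at 1 point is 62% instead of 79%.
- *Late-building effect.* Take differences of 0, 0, 0.4, 0.8, 1.2, 1.6 and 2.0 from 0h to 72h, with r = 0.5. Their sum of squares about the mean is 8.8 - 36/7 = 3.657, so λ = 16.5 × 3.657/3.125 = 19.3 and the interaction has 93% power. The adjusted mean, with an average difference of 1, has 79%.

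**The case against.** The strongest reply is that the planned analysis is adequate for the planned effect. At 2 points and correlation 0.5, both ANOVA tests exceed the planned 90%. This stands: low powers such as 44% and 30% arise only if the effect is half the planned one.

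Secondly, 0h is harmful only if the group effect decides. Section 24 speaks of changes and hypothesis 1 (Section 7) of reduction, which fits an interaction reading. There, 0h is what makes a constant effect visible: without it, the interaction has 5% power. This also stands, and it shows why the deciding test must be named.

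Thirdly, part of the gain comes from covariate adjustment and not from dropping 0h. At correlation 0.5, the variance ratio of 2.33 between the group effect with 0h and the adjusted contrast splits into 1.33 for removing 0h and 1.75 for adjustment. The adjustment part shrinks if the entry rule weakens the baseline correlation.

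Fourthly, SD 2.5 is a planning value. A reader might infer that normality cannot hold, but with a smaller SD and a mean near 3 a normality test would often pass. A reader might also infer that the fallback is a Mann-Whitney test at each time, with the multiplicity of six tests. The protocol does not say so; its general list also includes repeated-measures methods.

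None of this supplies a deciding test, a VAS-P fallback or agreement on 3h.

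**Conclusion.** The point holds, mainly because the primary test is not identified and its stated method is conditional, with no alternative assigned to VAS-P. On the Section 12 values the condition is likely to fail. Choosing between main effect and interaction after the fact would double the type I error to about 10%.

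The power argument is supporting. Under a constant effect and exchangeable correlation of 0.3 to 0.7, the baseline-adjusted contrast has more power than either ANOVA test. At 2 points, the shortfall below 90% is confined to the interaction at correlation 0.3 (77%) and, marginally, the group effect at 0.7 (89%). At 1 point the differences are large.

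It would be tempting to conclude that the trial is underpowered as planned, or that including 0h always wastes power. The documents support neither: the result depends on a correlation the protocol does not give, on the unnamed contrast and on the shape of the effect over time.

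**What to change.** In Section 24:

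- Pre-specify one primary contrast on the post-placement VAS-P scores with 0h VAS-P as covariate. An example is the group difference averaged over the post-placement times, from ANCOVA of each patient's mean or from a mixed model.
- Remove the normality condition, and add a rank-based or permutation check of the same contrast.
- Treat differences at single times as descriptive.
- Analyse IAP in the same way.
- Say in Section 12 that the 2-point difference refers to the chosen contrast.

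Reconcile the 3h assessment in the Section 35 schedule with Sections 19 and 24.

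**Cost.** No new data are needed, because 0h is already collected. Sections 24 and 34 name GraphPad Prism for the analysis, so other software may be needed. SPSS is named only for generating the random numbers (Section 13). An averaged contrast is less sensitive to an effect that builds up late. If that pattern is expected, the choice of contrast should reflect it, and it must be made before the data are seen.

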##### **Inclusion criteria**

- (1) Patients aged  $\geq 18$  years and  $\leq 65$  years.
- (2) Patients with a clear diagnosis of SAP.
- (3) Pain score (VAS-P) greater than 3.
- (4) Informed consent signed by the patient or his/her legal representative.

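### The missing-data rules for VAS-P put a pre-placement score into an imputed 1h value, have no answer at 72h and discard patients with two consecutive gaps; a mixed model on all observed scores should replace them

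*Protocol*

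**What the plan says.** Section 24 of the protocol deals with missing data in steps. Retrospective collection is tried first. For gaps regarded as random in a series of measurements, "we can estimate this by calculating the average of the time points before and after the missing" data. If two occasions in a row are missing, the patient's "data are considered incomplete and the patient will be excluded". For data not missing at random a method is to be picked, "such as the maximum deviation method or the Verbeke and Molenberghs method, on a case-by-case basis".

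Four other places bear on these rules:
- Section 19 sets the VAS-P times at 0h, 1h, 6h, 12h, 24h, 48h and 72h, with 0h before epidural placement. The schedule in section 35 adds a 3h assessment.
- The inclusion criteria in section 11 require "Pain score (VAS-P) greater than 3".
- The dropout criteria in section 11 cover placement shorter than 3 days, withdrawn consent, and inability to continue, for example because of a changed condition, discharge, or refusal of further evaluation.
- Section 24 analyses VAS-P at all these times by repeated measures ANOVA.

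**The concern.** These are stated rules, not gaps left for a later document, and they govern the only primary outcome.

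The neighbours of 1h lie on either side of the start of treatment, so an untreated score supplies half of a treated value. The times are unequally spaced, so a plain average of neighbours belongs to a different time from the one it fills. The last time has no later neighbour. The filled-in value then enters the ANOVA as if it had been observed.

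The exclusion rule throws away scores that were measured. A patient last seen at 24h lacks 48h and 72h and is removed, although five of seven scores exist. If leaving is related to pain or to arm, the patients who remain are no longer the groups that were randomised.

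**Working it through.** **Inputs from the protocol.** Section 12: two-sided α 0.05, power 90%, SD 2.5, effect 2 points, control means 1–3, experimental means 1–2, 15% dropout, 76 patients. Section 19: time points and the meaning of 0h. Section 11: entry score above 3.

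**Assumed, because the protocol does not give them.** Mean 0h score (4, 6 or 8), missing rates, within-patient correlation 0.5, and post-placement means of 3 (control) and 1 (experimental) that already apply at 1h. These two means are the pair within the section 12 ranges that gives the planned difference of 2.

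**1. The plan's own figure.** n = 2(1.9600 + 1.2816)² × 2.5² / 2² = 32.84, so 33 per group. 33 × 1.15 = 37.95, so 38 per group and 76 in total. The stated size is reproduced when σ² multiplies. Formula 1 as printed adds σ² and would give 6.8; that is a separate matter. The sample size does not depend on the present point.

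**2. One imputed 1h score.** With a common 0h mean B, the imputed means are (B + 3)/2 and (B + 1)/2. Their difference is −1.0 for any B, against a planned −2.0.

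| B | Control (excess) | Experimental (excess) | Contrast |
|---|---|---|---|
| 4 | 3.5 (+0.5) | 2.5 (+1.5) | −1.0 |
| 6 | 4.5 (+1.5) | 3.5 (+2.5) | −1.0 |
| 8 | 5.5 (+2.5) | 4.5 (+3.5) | −1.0 |

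Using 3h as the later neighbour changes nothing here, since it is also after placement.

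**3. Effect on the arm comparison.** If a share m of 1h scores is imputed in both arms, the 1h contrast is −2 + m: −1.95, −1.90 and −1.80 at 5%, 10% and 20%. At 10% the shift of 0.10, spread over six post-placement visits, is 0.10/6 ≈ 0.02. Unequal gaps matter more (B = 6):
- 5% control, 20% experimental: (1 + 0.20 × 2.5) − (3 + 0.05 × 1.5) = −1.58 at 1h.
- Reversed: (1 + 0.05 × 2.5) − (3 + 0.20 × 1.5) = −2.18 at 1h.

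**4. Spacing.** The midpoints of the neighbours are 3h for 1h, 6.5h for 6h, 15h for 12h, 30h for 24h and 48h for 48h. Only 48h is centred correctly. 72h has no later neighbour, so the average is undefined there.

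**5. How often the exclusion rule acts by chance.** With independent gaps at 5%, 10% or 15% per visit over seven visits, two in a row occur in 1.4%, 5.5% or 11.6% of patients.

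**6. Whether exclusion biases the contrast.** Simulation: 300,000 patients per arm, six visits, normal scores with SD 2.5, true contrast −2.0. Patients were removed whole, as a stand-in for the rule, either at random or with a probability that depends on their mean over the first four visits. Removal ran from 10% to 22% per arm.

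| Who is lost | Contrast in those kept |
|---|---|
| Completely at random | −1.99 (no bias) |
| High pain, both arms | −1.82 |
| High pain in control, random in experimental | −1.74 |
| Low pain, both arms | −1.83 |

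**7. Power.** Fewer patients alone: 90.1%, 87.3% and 84.9% at 33, 30 and 28 per arm. A shrunken contrast alone: the standard error at 33 per arm is 2.5 × √(2/33) = 0.6155. 1.74/0.6155 − 1.96 = 0.87 gives about 81%, and 1.83/0.6155 − 1.96 = 1.01 gives about 84%.

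**The case against.** The plan has mitigations. Retrospective collection comes first, and pain nurses also record scores (sections 9 and 34), so single gaps may be recoverable. Averaging is limited to random gaps and worded as an option. The 15% loss is already allowed for: 76 × 0.85 = 64.6, close to the planned 66. The method for data not missing at random is often left to a statistical analysis plan. All of this stands, and it limits the size of the problem. It does not make the averaging rule suitable at 1h or usable at 72h, and it does not justify discarding measured scores.

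The following stronger readings are tempting but unsupported:
- **That the rules bias the primary outcome in any case.** Exclusion does not if gaps are completely random. The direction is also not established: section 10 restricts the study to awake patients, and section 11 lists discharge beside a worsening condition. Losing high-pain patients from the experimental arm only would enlarge the contrast.
- **That the 1h error exceeds the planned effect.** An excess of 2.5 points in one imputed score is not comparable with a difference of 2 between group means. Both arms are inflated, and with equal gaps the contrast moves slightly toward no effect.
- **That the two-gap rule removes the whole planned 15%, about 11 of 76.** Many of these patients already meet the dropout criteria in section 11, so deleting the rule alone would not bring them back.
- **That standard errors are seriously understated.** At correlation 0.5 an averaged value has (1 + 0.5)/2 = 75% of the variance of an observed one. With 10% imputed and stable means, the visit-level standard error is √(0.975 × 0.90) = 0.94 of the available-case one, about 6% smaller.
- **That the case-by-case choice invites steering.** Section 14 keeps analysts blinded to assignment. What remains is that the method is chosen after the data are seen.

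**Conclusion.** The concern holds in a limited form, as a should-fix. Averaging across the placement boundary inflates an imputed 1h score and halves its contrast, but shifts the overall result by only about 0.02 points if 10% of 1h scores are missing equally in both arms. The average is mistimed at most other visits and undefined at 72h. Exclusion for two consecutive gaps wastes usable data. It costs only power under completely random gaps, and it can bias the comparison if gaps are related to pain or arm. The reasons for leaving in section 11 make such a link plausible, without proving it.

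The sizes rest on assumed missing rates, 0h means, correlation and dropout mechanisms. The simulated scores were not bounded to the scale, so −1.74 to −1.83 indicates an order of magnitude and is not a forecast. If the 1h means had not yet reached their later level, the 1h error would differ.

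**What to change.** 1. In section 24, delete the neighbour-averaging rule and the exclusion for two consecutive gaps.
2. In section 24, replace the repeated measures ANOVA for VAS-P with a likelihood-based mixed model for repeated measures. Use all observed post-placement scores, with terms for arm, visit and their interaction, the 0h score as a covariate, and no single imputation.
3. State that patients who meet the dropout criteria in section 11 still contribute the scores observed up to that point, except where consent to data use is withdrawn. Without this, step 1 changes little.
4. Replace the case-by-case choice with one sensitivity analysis fixed in advance, such as multiple imputation with a delta adjustment.
5. Reconcile sections 19 and 24 with the schedule in section 35 on the 3h assessment, so that the model's visits are defined.

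Cost: analysis wording, modest programming, and software that fits such a model. Whether the named package does so should be checked. No new data or patients are needed. The change should be made before outcome data are seen.
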